## APPENDICES

### A. Definitions

**Ascites:** Any abdominal fluid which is:

1. Mild, moderate or marked on ultrasound; or
2. Progressive on serial physical examinations; or
3. Requires diuretic therapy.

To meet the definition of ascites, abdominal fluid that is “mild” (“barely detectable”) on physical examination requires ultrasound confirmation that is “mild”, “moderate” or “marked” ascites. Ultrasound reports of minimal fluid around the liver do not meet the definition.

**Hepatic encephalopathy:** Any mental status alteration which is deemed by the investigator to be due to portosystemic encephalopathy, whether occurring during a provoked episode (GI bleeding, diuretics, usual sedative doses), or spontaneously (without apparent cause).

**Hepatocellular carcinoma:** A diagnosis of HCC will be based on either

1. Histology showing HCC (from a biopsy, surgery, or autopsy) or
2. A new hepatic defect on imaging with an AFP rising to > 1,000 ng/ml.

**Hepatorenal syndrome:** Progressive deterioration in renal function, with no other etiology, rising serum creatinine to > 1.5 mg/dl and at least one of the following;

1. Urine volume < 500 ml/d
2. Urine sodium < 10 mEq/l
3. Urine osmolality > plasma osmolality > 1

**Presumed Hepatocellular Carcinoma:** Presumed HCC will be considered when histology is not available and AFP is <1000 ng/ml, if:

1. A new hepatic lesion is shown on ultrasound and one additional imaging which shows a hepatic lesion with characteristics of HCC.
2. AFP >ULN and two imaging studies show a hepatic lesion with characteristics of HCC.
3. A progressively enlarging hepatic lesion starting as a new defect eventually resulting in the death of a patient.
4. A new hepatic defect with at least 1 characteristic scan and one of the following:
  - a. Increase in size over time (doubling in diameter or tripling in diameter if the initial size <1 cm when first discovered) or
  - b. An increasing AFP (values 3 months before or after the discovery of the defect by scanning) eventually rising to a level of >200 ng/ml and more than tripling the mean baseline value.

Images may include:

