**K. OUTCOME VARIABLES**

K.1. Primary Outcome Variables

The major outcome variable used in this study will be progression of liver disease as judged by any of the following outcomes:

K.1.a. Increase in Ishak fibrosis score by 2 points or more at 2 or 4 year biopsies

K.1.b. Death from any cause

K.1.c. Development of HCC

K.1.d. CTP score of 7 or higher at two consecutive study visits

K.1.e. Variceal hemorrhage

K.1.f. Ascites

K.1.g. Spontaneous bacterial peritonitis

K.1.h. Hepatic encephalopathy

K.2. Secondary Outcome Variables

Secondary outcome variables will include:

K.2.a. Quality of life,

K.2.b. Serious adverse events, and

K.2.c. Events requiring dose reductions (in both treatment groups).

K.2.d. Changes in fibrosis from baseline at year 2 or year 4 biopsy.

K.2.e. Presumed Hepatocellular Carcinoma

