**N. ADVERSE EVENTS**

**N.1. Definition**

N.1.a. An adverse event is any adverse change from the patient's baseline (pre-treatment) condition, including intercurrent illness which occurs during the course of the trial, after the consent form has been signed, whether the event is considered related to treatment or not.

N.1.b. A serious adverse event is an untoward medical occurrence that results in any of the following:

1. Death
2. Is life threatening (risk of death at the time of the event).
3. Requires in-patient hospitalization or prolongation of existing
4. hospitalization
5. Results in persistent or significant disability/incapacity
6. Congenital abnormality or birth defect

Important medical events that do not result in one of the events listed above may be considered a serious adverse event when, based upon appropriate medical judgment, they may jeopardize the patient and may require medical or surgical intervention to prevent one of the outcomes listed above.

N.1.c. A serious adverse event which is unexpected and is drug related (even remotely) will require expedited reporting (see N.3.a.).

N.1.d. The following events are trial outcomes and will not be considered to be serious adverse events:

1. Development of HCC or presumed HCC
2. A CTP score of 7 or higher at 2 consecutive study visits

3. Ascites
4. Variceal hemorrhage
5. Hepatic encephalopathy
6. Spontaneous bacterial peritonitis

N.2. Data collection procedures for adverse events

N.2.a. At each follow-up visit through Month 54, patients will be interviewed regarding medical conditions, medical changes, and symptoms that have occurred since the last visit. An Adverse Event form will be completed if any adverse event is reported. If the Study Coordinator or Principal Investigator learns of any hospitalizations or other adverse events between study visits, an Adverse Event form will be completed. All adverse events and Serious Adverse Events as of May 1, 2007 will not be reported to the DCC.

N.2.b. A Serious Adverse Event form will be completed for all adverse events rated as serious.

N.2.c. Patients will be followed for all ongoing unresolved adverse events until they are either resolved, or in the opinion of the Principal Investigator, the patient is medically stable.

N.3. Reporting procedures

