#### Q.1.j. Outcome Review Board (ORB)

An Outcome Review Board will be appointed to review all outcome events (Section K). Members of the Board will include Principal Investigators from the Clinical Centers. Clinical Centers will submit to the DCC the appropriate forms and source documents. Copies of these documents will be sent to two members of the ORB, and to a third if there is not consensus. Outcomes will be evaluated by the ORB based on pre-determined criteria for each outcome variable. ORB members will not know the treatment status of patients.

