1. MRI
2. triphasic CT
3. angiography (angiography taken prior to intra-arterial chemo-embolization may be used for this purpose if images are taken and reported prior to therapeutic intervention)
4. lipiodol scan
5. liver spleen scan with gallium

Characteristics of HCC include:

1. Hypervascularity
2. Arterial to portal vein shunts
3. Portal vein thrombosis near the defect
4. Tumor in the portal vein.

**Spontaneous bacterial peritonitis:** Any episode of spontaneous ascitic infection diagnosed on the basis of elevated neutrophil count ( $> 250/\text{ml}$ ) in paracentesis fluid or positive bacterial cultures and clinical diagnosis in the absence of WBC availability.

**Variceal hemorrhage:** A gastrointestinal hemorrhage which is believed by the investigator to be due to bleeding esophageal or gastric varices. In general, an endoscopy will have been performed and will have revealed either direct evidence of variceal bleeding (bleeding varix, red wale sign) or historical evidence for significant upper gastrointestinal bleeding plus upper endoscopy revealing moderate varices and no other site of bleeding is identified.

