## **C. Management Guidelines**

### **C.1. Depression**

#### Background

Mood disorders (i.e., depression and anxiety) are common and problematic side effects of IFN. Mood disorders may develop during the first few months of treatment or later during long term therapy. Mood disorders can develop in individuals without a prior psychiatric history and present with subtle signs and symptoms such as fatigue, withdrawn behavior, poor appetite, irritability, or sleep disturbance. Although IFN dose reduction and anti-depressant medications have proven useful, severe and life-threatening neuropsychiatric toxicity including attempted and completed suicide have been reported (1-3). Therefore, a heightened awareness of depression and its potential impact on patient safety and compliance is necessary when prescribing interferon.

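### Hepatic encephalopathy, a primary outcome component, is defined only by the attribution of an investigator who knows the arm, and no stated route takes a drug-attributed episode to masked review

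*Protocol*

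**What the plan says.** Protocol K.1 lists the events that each count as progression of liver disease. Two of them are "K.1.h. Hepatic encephalopathy" and "K.1.e. Variceal hemorrhage". Encephalopathy is also one of the five items in the CTP score (Appendix B), and a CTP score of 7 or more at two consecutive visits is a further primary component (K.1.d).

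Appendix A defines encephalopathy as "Any mental status alteration which is deemed by the investigator to be due to portosystemic encephalopathy", whether provoked or spontaneous. It defines variceal hemorrhage as "A gastrointestinal hemorrhage which is believed by the investigator to be due to bleeding esophageal or gastric varices", and adds: "In general, an endoscopy will have been performed and will have revealed either direct evidence of variceal bleeding".

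J.1.e puts the control arm on follow-up with no treatment, and no placebo is described. Q.1.j sets up the ORB. Two members review the documents that the centers submit, a third is added if they disagree, and members do not know the treatment. "Outcomes will be evaluated by the ORB based on pre-determined criteria for each outcome variable".

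Appendix C.1 says that mood disorders are common on interferon and can "present with subtle signs and symptoms such as fatigue, withdrawn behavior, poor appetite, irritability, or sleep disturbance". It also mentions severe neuropsychiatric toxicity. N.1.d lists encephalopathy under this rule: "The following events are trial outcomes and will not be considered to be serious adverse events".

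**The concern.** For encephalopathy the definition consists of the attribution. A change in mental status becomes a primary event when the site investigator assigns it to portosystemic encephalopathy, and that investigator knows who is on peginterferon. During randomized treatment a current drug explanation is available in one arm only.

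The same judgement also decides where the episode is recorded. Blamed on the liver, it is an outcome and is not a serious adverse event (N.1.d). Blamed on the drug, it is an adverse event. Masked review can correct a submitted event that should not count, but it cannot recover one that was not submitted.

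At stake is the comparison for hepatic decompensation (hypothesis C.2.a) and, through it, the composite. Fewer encephalopathy calls on peginterferon would look like benefit. Extra calls there, from drug effects read as encephalopathy, would hide benefit.

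**Working it through.** **How firmly Appendix A ties each event to something other than opinion**

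| Event | Anchor in Appendix A |
|---|---|
| Hepatocellular carcinoma | Histology, or new imaging defect with alpha-fetoprotein above 1,000 ng/ml |
| Spontaneous bacterial peritonitis | Neutrophil count in ascitic fluid, or positive culture with a clinical diagnosis |
| Ascites | Ultrasound grade, progression on serial examination, or need for diuretics |
| Variceal hemorrhage | Investigator's belief, with endoscopic findings expected in general |
| Hepatic encephalopathy | Investigator's attribution only |

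Encephalopathy is the one clinical event in this list with no anchor. In Appendix B it scores 1 (none), 2 (mild) or 3 (severe). One attribution therefore adds 1 or 2 CTP points, and a patient at 6 reaches the K.1.d threshold of 7 with a mild call if it persists to the next visit.

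**Routes to the ORB.** Q.1.j covers outcome events on forms and source documents from the centers. N.3.b sends deaths to the ORB on a Clinical Outcome form. N.3.a sends serious adverse events to the DCC, not to the ORB. No other route is described.

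**The plan's own figures.** Inputs from O.2: two-sided alpha 5%, 90% power, 18.7% control and 10.6% peginterferon at 3.5 years, 405 per arm.

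- Let d = p1 − p2, p̄ = (p1 + p2)/2, SE0 = √[2p̄(1 − p̄)/n] and SE1 = √{[p1(1 − p1) + p2(1 − p2)]/n}.
- Power = Φ[(d − 1.96·SE0)/SE1]. With d = 0.081, SE0 = 0.02485 and SE1 = 0.02469, power is 0.905, against the stated 90%.
- Events: 405 × 0.187 = 75.7 and 405 × 0.106 = 42.9, a difference of about 33.
- One patient changes an arm's rate by at most 1/405 = 0.25 points, and only if that patient has no other K.1 event.

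**Illustration 1: under-calling on peginterferon with no true effect.** The protocol gives no component rates, so the inputs here are assumptions. Both arms have a true rate of 18.7%. A share s of peginterferon-arm progressions rests only on investigator-attributed encephalopathy, and a fraction f = 50% of these goes uncounted. Then p2 = 0.187 × (1 − s·f), and two-sided rejection is Φ[(d − 1.96·SE0)/SE1] + Φ[(−d − 1.96·SE0)/SE1].

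For s = 10%: p2 = 0.187 × 0.95 = 0.1777, d = 0.00935, and SE0 and SE1 are both 0.02713. The terms are 0.0531 + 0.0106 = 6.4%.

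| s | Events lost (405 × 0.187 × s × 0.5) | Two-sided rejection (nominal 5%) |
|---|---|---|
| 5% | 1.9 | 5.3% |
| 10% | 3.8 | 6.4% |
| 20% | 7.6 | 10.7% |
| 30% | 11.4 | 18.4% |

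**Illustration 2: over-calling on peginterferon with the planned effect true.** Add k patients to the 10.6% arm, so p2 = 0.106 + k/405. With k = 4, p2 = 0.1159 and power falls from 0.905 to 0.81. With k = 8, p2 = 0.1258 and power is 0.67.

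**The case against.** The strongest reply is that the ORB already solves this. Two masked members judge each submitted case from source documents, with a third if they disagree, so for a submitted event site opinion does not decide alone. That stands, and it limits wrongly accepted events.

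A reader might go further than the documents allow in five ways:

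- **That the ORB's criterion is the site's attribution.** Q.1.j refers to pre-determined criteria and does not say that they are the Appendix A sentences. The Manual of Operations is not at hand. What can be said is that Appendix A is the only definition shown.
- **That drug-attributed episodes are never sent.** Q.1.j states no submission trigger. Serious adverse events in both arms reach the DCC, which compares patient data across forms (P.1.c). The supported statement is that no route to the ORB is described apart from deaths.
- **That variceal hemorrhage is equally exposed.** Its endoscopic findings largely anchor it. B.5 reports more thrombocytopenia with peginterferon but does not link it to bleeding, so the protocol names no competing drug explanation for a bleed.
- **That the bias must favor peginterferon.** Over-calling is also possible.
- **That a given share of the planned effect is at risk.** Multiplying 0.25 points by an assumed number of episodes treats each patient as having no other K.1 event. Many will have one, and then only the timing changes, or nothing.

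Two further points have some force. The signs quoted from Appendix C.1 describe mood disorder, and no passage says that they resemble encephalopathy. The definition also counts provoked episodes, so a drug precipitant does not by itself exclude an event. Both narrow the overlap. Neither removes it, because the definition accepts any mental status change and leaves the cause to the investigator.

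**Conclusion.** The point holds for hepatic encephalopathy. A component that alone meets the primary outcome has no criterion in the protocol beyond an unmasked attribution. A competing explanation exists in the treated arm, and the protocol describes no way for masked reviewers to see episodes explained that way, deaths excepted. Ascertainment can differ by arm in either direction.

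The size cannot be derived from the protocol. Under the stated assumptions, losing about 2 to 4 events leaves the two-sided error at 5.3% to 6.4%. It takes about 8 to 11 lost events, out of 76, to reach 10.7% to 18.4%. The distortion of the composite is small unless encephalopathy-only cases are a sizeable share of first progressions and many are misdirected. The correction is worth making because it is cheap. The finding does not show that the primary result would be wrong. The sample size is not in question. Variceal hemorrhage needs at most the same change of wording.

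**What to change.** 1. **Appendix A.** Define hepatic encephalopathy as judged by the masked ORB from source documents, in place of the investigator's attribution. The same wording could be used for variceal hemorrhage, keeping its endoscopic findings.
2. **Q.1.j, intake.** Have the DCC select cases from the Adverse Event and Serious Adverse Event forms, in both arms and whatever cause the site assigned. The selection is every serious event or hospitalization with altered mental status, and every adverse event of confusion, disorientation or altered consciousness. Mood symptoms alone are left out. Without that limit, common interferon mood effects would fill the ORB's workload mostly from one arm and hint at treatment.
3. **Q.1.j, masking.** State that treatment information is redacted from the packets. The section says that members will not know the treatment but not how the documents are masked.

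The forms already exist. N.2.a collects adverse events through Month 54 and stops reporting to the DCC as of May 1, 2007. Randomized treatment ends in January 2007 (A.2), so the treated period is covered. The cost is wording in two places, a modest number of extra ORB packets and some redaction work. No patient procedure is added.

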1. MRI
2. triphasic CT
3. angiography (angiography taken prior to intra-arterial chemo-embolization may be used for this purpose if images are taken and reported prior to therapeutic intervention)
4. lipiodol scan
5. liver spleen scan with gallium

Characteristics of HCC include:

1. Hypervascularity
2. Arterial to portal vein shunts
3. Portal vein thrombosis near the defect
4. Tumor in the portal vein.

**Spontaneous bacterial peritonitis:** Any episode of spontaneous ascitic infection diagnosed on the basis of elevated neutrophil count ( $> 250/\text{ml}$ ) in paracentesis fluid or positive bacterial cultures and clinical diagnosis in the absence of WBC availability.

**Variceal hemorrhage:** A gastrointestinal hemorrhage which is believed by the investigator to be due to bleeding esophageal or gastric varices. In general, an endoscopy will have been performed and will have revealed either direct evidence of variceal bleeding (bleeding varix, red wale sign) or historical evidence for significant upper gastrointestinal bleeding plus upper endoscopy revealing moderate varices and no other site of bleeding is identified.

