F.1.g. Steatohepatitis (alcohol or non-alcoholic), defined as severe histologic changes to include all of the following 3 criteria:

1. Steatosis (marked);
2. Mallory bodies (many);
3. Zone 3 pericellular fibrosis (extensive).

F.1.h. Drug-induced liver disease

- F.2. A Child-Turcotte-Pugh score of greater than or equal to 7 points or any history of ascites, or any history of hepatic encephalopathy, or current evidence of ascites as defined in Appendix A. See Appendix B for a definition of the CTP score and for an adjustment to this score for patients with Gilbert's syndrome.
- F.3. Any documented history of bleeding from either esophageal or gastric varices.
- F.4. A platelet count of less than 50,000/mm^3. Pre-treatment or screening platelet count values may be used by the Express Group for eligibility requirements.
- F.5. A neutrophil count of less than 1,000/mm^3. Pre-treatment or screening neutrophil count values may be used by the Express Group for eligibility requirements.
- F.6. A hematocrit of less than 33% or hemoglobin less than 11 gm/dL. Pre-treatment or screening hematocrit and hemoglobin values may be used by the Express Group for eligibility requirements.
- F.7. An alpha-fetoprotein of greater than 200 ng/mL for Lead-in patients, and an AFP of greater than 1000 for Express patients.
- F.8. Evidence of an hepatic mass lesion by either ultrasound, CT or MR scan that is suspicious for hepatocellular carcinoma.
- F.9. Renal insufficiency defined by a serum creatinine greater than 1.5 mg/dL.
- F.10. A positive test for HIV confirmed by Western blot obtained within the past 12 months. HIV testing will be performed using standard protocols for confidentiality and notification of health authorities. A standard separate consent HIV testing consent form will be used at all participating centers.
- F.11. Diabetes that, in the opinion of the investigator, is not controlled by diet, an oral hypoglycemic agent, and/or insulin.

- F.12 Patients with hemophilia.
- F.13. Patients who have received an organ, limb or bone marrow transplant.
- F.14. Patients who require the use of certain chronic medications such as immunosuppressive medications (corticosteroids, methotrexate, azathioprine) or coumadin should be off medications for six months or longer before being screened.
- F.15. Patients with active systemic autoimmune disorders such as rheumatoid arthritis, systemic lupus, etc.

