**L. CESSATION OF TREATMENT**

L.1. Outcomes which require permanent discontinuation of treatment:

L.1.a. Death from any cause

L.1.b. Liver transplant

L.1.c. HCC

L.1.d. UNOS Status 2b as defined by the 1999 UNOS Transplant Criteria Meeting:

1. Presence of a small hepatocellular carcinoma; or
  2. CTP score of 10 or more; or
  3. CTP score of 7 or more plus any of the following:
    - Documented unresponsive variceal hemorrhage
    - Hepatorenal syndrome
    - Occurrence of one episode of spontaneous bacterial peritonitis
    - Refractory ascites unresponsive to treatment
- L.2. By these criteria, onset of ascites, variceal hemorrhage, or hepatic encephalopathy do not require discontinuation of peginterferon alfa-2a but may lead to withholding further therapy if, in the opinion of the investigator, continuation is not in the patient's best interest.
- L.3. Randomized patients who stop receiving peginterferon alfa-2a will continue to be followed at regular visit intervals for the duration of the trial (if possible). Patients who discontinue treatment during the Lead-in Phase will not be followed beyond 24 weeks except for follow-up on all unresolved adverse events.

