P.4.d. If missing data are minimal, then the percent of patients having an outcome at the end of four years can be compared using logistic regression. This method will have less power than methods based on survival analysis. Several methods have been proposed for the analysis of interval-censored survival data (175-178). The method to be used will be described in detail in the Manual of Operations (MOO).

P.4.e. Hepatic events will be evaluated using life table methods and proportional hazards regression (45). The primary analysis will be life table analyses of time to first event. Life table estimates of time to hepatic event will be calculated for the two treatment groups with clinical center and baseline presence or absence of cirrhosis as strata. The log rank test will be used to test the difference between the treatment groups.

P.4.f. Analyses will be conducted for all hepatic events and the subset of death, HCC, or UNOS status 2b as defined in 1999.

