| <250                                       | Stop Drug                                                                                                                                                                        |
| Platelet Count
(cells/mm  ) |                                                                                                                                                                                  |
| ≥50,000                                    | None                                                                                                                                                                             |
| 35,000 - 49,000                            | Delay or hold dose until ≥50,000 then resume dose with 1 Level adjustment                                                                                                        |
| 25,000 - 34,000                            | Delay or hold dose until ≥50,000 then resume dose with 2 Level adjustment                                                                                                        |
| <25,000                                    | Stop Drug                                                                                                                                                                        |

\*Week 1-2: Signifies the abnormality was noted within the first 2 weeks of the initiation of test drug treatment.

\*\*Week 3 and greater: Signifies the abnormality was noted more than 2 weeks following the initiation of test drug treatment.

**c. Dose Adjustments for Low Absolute Neutrophil and Platelet Counts for patients who enter the trial with neutrophils between 1,000/mm^3 to 1,500/mm^3 and Platelet Count from 50,000/mm^3 up to 75,000/mm^3.**

| Platelet Count
(cells/mm^3) | Downward Dose Adjustment                                                      |
|--------------------------------------------------|--------------------------------------------------------------------------------------|
| ≥40,000                                          | None                                                                                 |
| 20,000 - 40,000                                  | Delay or hold dose for 1 week until ≥40,000 then resume dose with 1 Level adjustment |

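### The ascitic neutrophil cut-off for spontaneous bacterial peritonitis is printed per ml, equal to 0.25 cells per mm³: an apparent unit error, with narrow exposure through UNOS status 2b

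*Protocol*

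**What the plan says.** Protocol Appendix A (Definitions) describes SBP as "Any episode of spontaneous ascitic infection diagnosed on the basis of elevated neutrophil count". The full criterion reads "elevated neutrophil count ( $> 250/\text{ml}$ ) in paracentesis fluid". A second route, positive cultures with a clinical diagnosis, applies when no white-cell count is available. No other section gives a threshold for ascitic fluid.

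Where the protocol gives a unit for neutrophil or platelet limits elsewhere, it is per mm³:
- F.5 excludes "A neutrophil count of less than 1,000/mm 3".
- F.4 excludes "A platelet count of less than 50,000/mm 3".
- H.1.d and H.1.e use per mm³ for the starting-dose strata.
- Appendix D4, table c, covers "patients who enter the trial with neutrophils between 1,000/mm 3 to 1,500/mm 3".

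SBP is used in three places:
- K.1.g makes it a component of the primary outcome.
- L.1.d, on permanent discontinuation, lists "Occurrence of one episode of spontaneous bacterial peritonitis" among the items that, added to a CTP score of 7 or more, give UNOS status 2b. Appendix A repeats that definition.
- P.4.f states: "Analyses will be conducted for all hepatic events and the subset of death, HCC, or UNOS status 2b as defined in 1999".

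L.2 says that onset of ascites does not by itself require discontinuation. Q.1.j sends Section K outcomes to an Outcome Review Board (ORB) that is blind to treatment and works from criteria fixed in advance.

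**The concern.** A threshold described as elevated should separate infected from uninfected fluid. A limit below one cell per mm³ can hardly do that, and the unit is out of line with the rest of the protocol. The natural explanation is that the unit was set down wrongly.

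The number matters because the protocol treats SBP and ascites differently. Ascites counts towards status 2b only when it is refractory, and its onset does not require stopping treatment. One SBP episode with CTP of 7 or more does give status 2b. If the cell-count criterion does not discriminate, the line between the two is weaker than intended. That line bears on a stopping rule, which can act only on patients receiving peginterferon, and on a secondary analysis in which ascites alone does not count. Centres that read the unit literally and centres that read through it could also classify the same fluid differently.

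**Working it through.** **Inputs.** SBP cut-off: 250 per ml (Appendix A). Lower limit for blood neutrophils at entry: 1,000 per mm³ (F.5). Conversion: 1 ml = 1,000 mm³.

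**Step 1, convert the printed figure.** 250 per ml ÷ 1,000 mm³ per ml = 0.25 per mm³.

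**Step 2, compare with the same number in the protocol's usual unit.** 250 per mm³ × 1,000 = 250,000 per ml, and 250,000 ÷ 250 = 1,000. The factor of 1,000 is relative to the same number carrying the other unit. The protocol does not state that second figure, and it is not put forward here as the right one.

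**Step 3, compare with a limit the protocol does state.** 1,000 ÷ 0.25 = 4,000, so the printed cut-off is 1/4,000 of the blood neutrophil count below which a patient is excluded for having too few. The fluids differ, so this tests plausibility only.

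**Step 4, follow the threshold into the analyses.**
- *Primary composite (K.1, with the time-to-first-event analysis in P.4.e).* SBP presupposes ascitic fluid. Ascites is an event under K.1.f, and CTP of 7 or higher at two consecutive visits is an event under K.1.d. Most patients who could be affected have therefore already had an event, or have one at about the same time.
- *Sample size (O.2).* It rests on overall annual progression rates. No SBP rate enters, so nothing changes.
- *UNOS status 2b (L.1.d and P.4.f).* A CTP of 10 or more, or a small hepatocellular carcinoma, gives 2b without SBP. The threshold can change the classification only where CTP is 7 to 9, fluid has been tapped, the count lies between 0.25 per mm³ and the intended cut-off, the episode is diagnosed as infection, and no other 2b item is met. In P.4.f, patients who have already died or developed hepatocellular carcinoma are counted anyway.

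**Step 5, size.** The protocol gives no expected number of paracenteses and no distribution of CTP scores over follow-up. The effect on L.1.d and P.4.f is bounded by the number of patients meeting the conditions in step 4, and that number cannot be derived.

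**The case against.** **It may be a reading artefact.** The unit sits inside a machine-read mathematical string, and units elsewhere are not always clean: B.3 gives an interferon dose with a bare µ where E.3 uses mU. This stands in part and cannot be settled from the text at hand. Against it, the string reads ml plainly, and the micro sign survives in the peginterferon doses, including the same kind of string in H.1.d. The original page must be looked at first.

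**There is no contradiction.** This stands. A reader might infer that the protocol states two SBP thresholds 1,000-fold apart. It states one. The per-mm³ figures are blood counts used for eligibility and dosing, so the evidence is an implausible value and an unusual unit.

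**Ordinary ascites would not become SBP.** A reader might infer that almost any tapped ascites with CTP of 7 or more would count as SBP, inflating P.4.f and forcing discontinuations. The documents do not support that. The definition requires a diagnosed infection of the ascitic fluid, so a count alone does not qualify, and two blinded ORB members, with a third if they disagree, review each outcome. What remains is that the ORB works from pre-set criteria, so a wrong unit could be carried into them, and the protocol does not say that the L.1.d decision passes through the ORB.

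**Clinicians would read through it.** Probably so. That limits the harm, but it leaves an outcome definition dependent on readers overriding what is printed.

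**Conclusion.** The point holds as an apparent unit error in a decision threshold and is minor. As printed, the cut-off is 0.25 neutrophils per mm³, which does not fit the word elevated or the unit used for the protocol's other neutrophil and platelet limits.

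It would be wrong to conclude that the primary result is at risk merely because SBP is a primary component. Ascites and repeated CTP of 7 or higher already capture most such patients in the first-event analysis, and sample size and power are untouched. The remaining exposure is the 2b route into L.1.d and P.4.f. It is narrow, it is limited by the need for a diagnosed infection and, for outcomes, by ORB review, and it cannot be quantified from the protocol.

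The conclusion assumes that the unit was read correctly from the page, and that the ORB criteria and the Manual of Operations, neither of which is at hand, do not already carry a different unit. No view is taken on which clinical threshold is right.

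**What to change.** 1. Check the unit in Appendix A on the original page. If it is a reading error, nothing further is needed.
2. If it is printed as shown, reconcile it with the source of the definition and with the unit used for the protocol's other cell counts.
3. Carry the reconciled definition into the ORB criteria, K.1.g, the status 2b items in L.1.d and Appendix A, and the P.4.f subset.
4. Re-check any SBP already adjudicated on a cell count, and any status 2b classification that rested on it.

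The cost is one corrected unit, handled through the protocol-change approvals in Q.2, and a short review of what is likely to be a small set of events. The clinical threshold is for the investigators to confirm from their source; none is proposed here.
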